### Power of the study

Based on retrospective data of 399 patients who underwent MAS, we assessed all mortality and morbidity due to major complications (multiple reoperations, multiple percutaneous drainages, enterostomy during re-intervention) and found this to be 17 %. Based on the results of den Dulk, who report a decrease in mortality following implementation of a clinical item scoring list, we calculated the following sample size [6]: a group sample size of 525 in group 1 and 525 in group 2 to achieve 80 % power to detect a difference in frequency of morbidity in the control group, which is 17 %, in comparison to the PRECious group, with an expected morbidity of 11 %. The test statistic used is the two-sided Mantel-Haenszel test. The significance level of the test was targeted at 0.05.

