### Participating surgeons and clinics

Seven Dutch hospitals will participate in the study; one academic and six teaching centers: VU medical center, Amsterdam; Slotervaart ziekenhuis, Amsterdam; Medisch Centrum Alkmaar, Alkmaar; Rode Kruis Ziekenhuis, Beverwijk; Spaarne Gasthuis, Haarlem; Westfries Gasthuis, Hoorn and Zaans Medisch Centrum, Zaandam. All participating surgeons have ample experience within their respective field. This is of importance because complication rates and morbidity are associated with learning curves and might therefore affect the primary outcome [39].

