### Patient allocation and design

Patients will be informed about the study at the outpatient clinic. The patient will be included upon admission after informed consent has been obtained. Due to the nature of the study, a parallel-randomized design is not the preferred option, because this would allow for bias by crossover and automated CRP and CT enquiries by physicians in both patient groups. A cluster design is not deemed feasible due to differences between the participating centers (i.e., academic and teaching hospitals). A stepped-wedge design is deemed appropriate. Due to the large number of participating centers, little bias is expected from other changes in treatment. Changes will be monitored and corrected for if applicable. Thus, the two groups will be compared according to two periods. Patients allocated to the first period will receive standard on-demand additional examinations. After a transition phase of one month allowing for implementation, all patients will be allocated to the intervention arm and will receive standardized postoperative monitoring of serum CRP levels on POD 3, 4 and 5. If CRP levels exceed 140 mg/L additional CT will be conducted.

Data collection will be via an online module, which allows for inclusion and data collection. Participating surgeons will be able to log in to the secured module via the PRECious trial website. After completing the inclusion form, an immediate response with a code number and type of postoperative control protocol will be obtained.

The nature of the study does not allow for blinding, because it would not be ethical to perform sham venous puncture, and the protocol will be known by the attending physician to allow CT to be arranged. Instead of blinding, the add-on value of CRP measurements will be tested. The attending physician will have to grade the patient in the morning before CRP levels are known, grade 1 indicating a healthy patient, grade 10 a patient at acute risk of death. The physician will also have to state whether he/she would perform CT prior to CRP levels being measured, allowing for assessment of the add-on value of the presented standardized quality control algorithm.

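### The 80% power for 525 + 525 patients is the figure for independent patients in two groups; it makes no allowance for the stepped-wedge design named for the trial, and with calendar-time adjustment it is not reached in any layout tried

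*Protocol article*

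**What the plan says.** The section Power of the study sets "a group sample size of 525 in group 1 and 525 in group 2 to achieve" its target. It words that target as "80 % power to detect a difference in frequency of morbidity in the control group". The control rate is stated as "in the control group, which is 17"%, and the PRECious group is planned "with an expected morbidity of 11"%. On the test it says: "The test statistic used is the two-sided Mantel-Haenszel test". On alpha: "The significance level of the test was targeted at 0.05". The paragraph mentions no hospital effect and no calendar-time effect.

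Elsewhere the design is a different one. Participating surgeons and clinics states: "Seven Dutch hospitals will participate in the study". Patient allocation and design states: "A stepped-wedge design is deemed appropriate". The same section then describes comparing the two groups as two periods, with a one-month transition between them, and corrects for other changes in treatment only where this is thought applicable. Data collection and statistics names chi-square or McNemar tests for frequencies.

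**The concern.** In a stepped wedge, every hospital moves from control to intervention, so later patients are more often intervention patients. The treatment effect has to be separated from calendar time, and that costs information even if hospitals do not differ at all. A sample size for independent patients leaves this cost out.

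The 80% is therefore attached to a design other than the one named. If the real power is well below it, a true fall from 17% to 11% could easily be missed, and a null result would be read as absence of benefit on the strength of a power the trial never had. The Trial status section says recruitment has not started, so the statement can still be put right.

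**Working it through.** **1. The plan's own figure.** Inputs from Power of the study: 0.17, 0.11, two-sided 0.05, power 80%; mean rate 0.14. The pooled two-proportion formula is

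n = [1.96 √(2 × 0.14 × 0.86) + 0.842 √(0.17 × 0.83 + 0.11 × 0.89)]² / 0.06² = 523.8, so 524 per group.

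Power at 525 per group is 80.1%. The figure reproduces without any term for hospital or time.

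**2. Layout assumed for a stepped wedge.** Not in the readable text, so assumed: seven steps with one hospital each, eight periods, equal cells of 1,050/56 = 18.75 patients, and constant within-hospital correlation. The ICC range 0 to 0.10 is also an assumption. Total variance is 0.14 × 0.86 = 0.1204. Power = Φ(0.06/SE − 1.96), with no small-sample correction for seven hospitals.

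**3. Time-adjusted power.** The Hussey-Hughes variance (fixed periods, random hospital) is

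Var = I s (s + T t) / [(IU − W) s + (U² + ITU − TW − IV) t],

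where s = (1 − ICC) × 0.1204/18.75 and t = ICC × 0.1204. For this layout I = 7, T = 8, U = 28, W = V = 140. So IU − W = 56, and the second bracket is 784 + 1,568 − 1,120 − 980 = 252.

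- ICC 0: s = 0.00642; Var = 7s/56 = 0.000803; SE = 0.0283.
- ICC 0.01: s = 0.006357, t = 0.001204; Var = 7 × 0.006357 × 0.015989 / (0.3560 + 0.3034) = 0.001079; SE = 0.0328.
- ICC 0.05: s = 0.006100, t = 0.00602; Var = 7 × 0.006100 × 0.05426 / (0.3416 + 1.5170) = 0.001247; SE = 0.0353.

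The variance implied by the plan is 4 × 0.1204/1,050 = 0.000459. The detectable difference at 80% power is 2.80 × SE.

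| ICC | Power | Variance ratio | Detectable difference |
|---|---|---|---|
| 0 | 56.3% | 1.75 | 7.9 points |
| 0.01 | 44.7% | 2.35 | 9.2 points |
| 0.02 | 41.7% | 2.56 | 9.6 points |
| 0.05 | 39.7% | 2.72 | 9.9 points |
| 0.10 | 40.2% | 2.68 | 9.8 points |

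The ICC 0 row contains no clustering, so its loss comes only from separating treatment from time.

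**4. Other time-adjusted layouts, same 1,050 patients.**
- Three steps of two, three and two hospitals: 33-43%. Steps of three, two and two: 35-47%.
- Two steps (three and four hospitals): 28-36%.
- Seven steps with unequal hospital sizes (one assumed spread): about 48-61% at ICC 0 and 40-45% at ICC 0.01.

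**5. Without time adjustment.**
- Staggered crossing in seven steps, random-hospital model: 72-80% over ICC 0 to 0.10.
- All hospitals switching together at the halfway point: 80% at ICC 0, 80.4% at 0.01, 82% at 0.05.
- Mantel-Haenszel test stratified by hospital, seven steps: the information is Σ 18.75 × k(8 − k)/8 for k = 1 to 7, which is 18.75 × 84/8 = 196.9. SE = √(0.1204/196.9) = 0.0247 and power is 68%.

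These are chances of a significant before-versus-after difference. They are power for the intervention only if nothing else changes over time. With a common switch and a period term the model is singular, so no time-adjusted effect exists to be estimated.

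**The case against.** The strongest defence is that the article does not commit to the analysis assumed in the time-adjusted figures. It describes a comparison of two periods, puts all patients of the first period in the control group and all of the second in the intervention group, and adjusts for other changes only if applicable. No staggered order of hospitals appears in the readable text. For a common halfway switch without a time term, the nominal 80% survives, because each hospital serves as its own control.

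That part stands, and it limits the point. A reader might infer that the trial as planned delivers 40-56% power. The documents do not support that: the steps, cell sizes, ICC and time adjustment behind those figures are all assumed, and the design flow chart (Fig. 1) is not shown. Nor is the arithmetic wrong; it reproduces. The absence of a step count or a loss allowance from a journal article is not itself a fault, since the full protocol may hold them.

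The defence does not rescue the 80%, though. Under a two-period comparison without time adjustment, any trend in surgical care is credited to the intervention, and the article's Discussion itself describes a time of advancing technique and fast-track care. If all hospitals switch together, the study is a before-after comparison and not the stepped wedge that is named.

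**Conclusion.** The point holds in conditional form. The 525 + 525 patients and 80% power are the individually randomised figure and do not describe the named design.

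- **With time adjustment**, one hospital per step, eight equal periods and 1,050 patients, power for 17% versus 11% is about 56% at ICC 0, 45% at 0.01 and 40% at 0.05 to 0.10. Three or two steps bring it to about 28-43% (up to 47% if three steps are split three, two and two). No time-adjusted layout tried came near 80%; the highest was about 61%, with unequal hospitals at ICC 0.
- **Without time adjustment**, nominal power is about 72-82% under a random-hospital model (68% with a hospital-stratified test and seven steps). The fault is then confounding with calendar time rather than low power.

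That the stated figure ignores hospital and time is certain. The size of the shortfall depends on a layout and ICC that the sponsor has to supply.

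**What to change.** Rewrite the power paragraph for the design actually used:

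- State the number of steps, the hospitals per step, the expected patients per hospital-period and an ICC range.
- Name a time-adjusted model with a hospital effect as the primary test, and bring the tests named under Data collection and statistics into line with it.
- Report power for 17% versus 11%, and the detectable difference, at 1,050 patients. Drop the 80% claim unless that calculation supports it.
- If all hospitals are to switch at once, call the study a before-after comparison and say that its effect cannot be separated from calendar time.

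The cost is one paragraph, a matching analysis sentence and a less favourable stated power. The correction itself adds no patients. If the sponsor wants to keep 80%, the seven-step layout above would need about 1,840 patients in total at ICC 0 and about 3,010 at ICC 0.05. That is a separate decision, best taken before recruitment starts.

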### Inclusion criteria

All adult patients who are to undergo elective MAS can be included in the study. MAS will be defined as all gastrointestinal resections with reconstruction with anastomosis and/or stoma. For instance, cholecystectomy will not be included because no anastomosis or stoma is performed. Written informed consent will be obligatory.

### Exclusion criteria

Patients who undergo emergency surgery as a primary operation will be excluded to allow for appropriate informed consent. Patients with an American Society of Anaesthesiologists (ASA) classification of four of higher will be excluded. As CT may be performed if CRP levels exceed 140 mg/L, patients with pre-operative impaired renal function (glomerular filtration rate <60) (within 4 weeks before surgery) will be excluded. Also patients with allergy to contrast medium will be excluded.

### Participating surgeons and clinics

Seven Dutch hospitals will participate in the study; one academic and six teaching centers: VU medical center, Amsterdam; Slotervaart ziekenhuis, Amsterdam; Medisch Centrum Alkmaar, Alkmaar; Rode Kruis Ziekenhuis, Beverwijk; Spaarne Gasthuis, Haarlem; Westfries Gasthuis, Hoorn and Zaans Medisch Centrum, Zaandam. All participating surgeons have ample experience within their respective field. This is of importance because complication rates and morbidity are associated with learning curves and might therefore affect the primary outcome [39].

### Patient allocation and design

Patients will be informed about the study at the outpatient clinic. The patient will be included upon admission after informed consent has been obtained. Due to the nature of the study, a parallel-randomized design is not the preferred option, because this would allow for bias by crossover and automated CRP and CT enquiries by physicians in both patient groups. A cluster design is not deemed feasible due to differences between the participating centers (i.e., academic and teaching hospitals). A stepped-wedge design is deemed appropriate. Due to the large number of participating centers, little bias is expected from other changes in treatment. Changes will be monitored and corrected for if applicable. Thus, the two groups will be compared according to two periods. Patients allocated to the first period will receive standard on-demand additional examinations. After a transition phase of one month allowing for implementation, all patients will be allocated to the intervention arm and will receive standardized postoperative monitoring of serum CRP levels on POD 3, 4 and 5. If CRP levels exceed 140 mg/L additional CT will be conducted.

Data collection will be via an online module, which allows for inclusion and data collection. Participating surgeons will be able to log in to the secured module via the PRECious trial website. After completing the inclusion form, an immediate response with a code number and type of postoperative control protocol will be obtained.

The nature of the study does not allow for blinding, because it would not be ethical to perform sham venous puncture, and the protocol will be known by the attending physician to allow CT to be arranged. Instead of blinding, the add-on value of CRP measurements will be tested. The attending physician will have to grade the patient in the morning before CRP levels are known, grade 1 indicating a healthy patient, grade 10 a patient at acute risk of death. The physician will also have to state whether he/she would perform CT prior to CRP levels being measured, allowing for assessment of the add-on value of the presented standardized quality control algorithm.

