### Data collection and statistics

Data will be collected partially by means of a secured Internet module and partially by hard-copy datasheets. The secured online module is especially designed for the PRECious trial. Hard-copy datasheets, such as completed quality of life questionnaires will be sent to the VU medical center by mail, were they will be kept in a secured room. Data will be collected daily until discharge. PROMs will be collected preoperatively, and at 5 days, 3 months and 12 months postoperatively. A study chart for measurements is depicted in Table 1.

**Table 1 Tab1:** Study measurements

	Study period										
	Enrolment	Allocation	Post-allocation								Close-out
Time point	Pre-operative	Pre-operative	Surgery	POD 2	POD 3	POD 4	POD 5	Discharge	3 Mo	12 Mo	t_x_
Enrolment											
Eligibility screen	X										
Informed consent	X										
Allocation		X									
Interventions											
Control group		X									
CRP measurement				X	X	X	X				
QOL questionnaire		X					X		X	X	
PRECious group											
CRP measurement				X	X	X	X				
CT if CRP >140 mg/L					X	X	X				
QOL questionnaire		X					X		X		
Assessments											
Control group											
List baseline variables		X									
List operative data			X								
List admission data								X			
Quality of life		X					X		X	X	
List morbidity								X	X	X	
List survival								X	X	X	
PRECious group											
List baseline variables		X									
List operative data			X								
List admission data								X			
Quality of life		X					X		X	X	
List morbidity								X	X	X	
List survival								X	X	X	X

*POD* postoperative day, *Mo* months, *CRP* C-reactive protein, *CT* computed tomography scan, *QOL* Quality of Life, T_x_ end of protocol

One research fellow in the VU medical center will monitor the data for all included patients, and maintain regular contact with all participating centers. Due to the nature of the study the researcher cannot be blinded, hence an external monitoring committee (Clinical Research Bureau, Amsterdam, Netherlands) is installed and will assess data collection. All required parameters will be collected in an SPSS data file. Data analysis will be performed according to the intention-to-treat principle. Continuous variables will be compared using the *t* test or Mann-Whitney *U* test, as appropriate. Frequencies will be compared using the Chi-square or McNemar tests, as appropriate.

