#### Standard group

In the first period all patients will be allocated to the control group and will receive standard postoperative monitoring, which consists of daily measurement of clinical parameters (heart rate, blood pressure, temperature, pain) and assessment of the patient by the attending physician. Additional examinations such as blood sampling and imaging will only be conducted on demand, for instance, if clinical parameters deviate or physical examination shows signs of complications.

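### Patients are enrolled individually into open-label periods that already reveal the arm, and the stated tests use no covariates, so a case-mix shift between periods would distort the result

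*Protocol article*

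**What the plan says.** **Enrolment.** Consent is individual and mandatory: "Written informed consent will be obligatory" (Inclusion criteria). Patients first hear of the study before admission: "Patients will be informed about the study at the outpatient clinic" (Patient allocation and design). The same section then says: "The patient will be included upon admission after informed consent has been obtained".

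**Allocation.** The arm follows from the date. For the first period: "In the first period all patients will be allocated to the control group and will receive standard postoperative monitoring" (Standard group). For the second: "After a transition phase of one month allowing for implementation, all patients will be allocated to the intervention arm" (Patient allocation and design). The online module reveals the arm last: "After completing the inclusion form, an immediate response with a code number and type of postoperative control protocol will be obtained". The trial is open label.

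**Comparison.** Patient allocation and design compares the two groups as two periods. Data collection and statistics states: "Frequencies will be compared using the Chi-square or McNemar tests, as appropriate". Power of the study names a two-sided Mantel-Haenszel test and no stratification factor. The only correction mentioned, in Patient allocation and design, is for other changes in treatment, where applicable.

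**The concern.** Putting consent before the module's reply looks like concealment, but everyone at the site knows which period is running. Surgeon and patient therefore know the arm when they decide on participation.

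What they are deciding about also differs. The PRECious group section expects CT in two thirds of PRECious patients against one third of controls, with intravenous contrast and, depending on the organ operated on, oral or rectal contrast. The kind of patient who is asked, or who agrees, could change at the switch.

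A test without covariates attributes any resulting difference in baseline risk to the algorithm. The primary conclusion is at stake, in either direction: an apparent benefit produced by lower-risk enrolment, or a real benefit hidden by higher-risk enrolment.

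**Working it through.** **1. The plan's own sample size.** Inputs from Power of the study: 17% against 11%, two-sided 0.05, 80% power, 525 per group. With mean rate 0.14:

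n = [1.96·√(2·0.14·0.86) + 0.842·√(0.17·0.83 + 0.11·0.89)]² / 0.06² = 523.8, so 524 per group.

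The stated 525 is reproduced, with power 80.1%. The arithmetic is sound. It is that of a plain two-proportion comparison of comparable groups, with no term for case mix, centre or period.

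**2. Does anything stated deal with a case-mix shift?**

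- The module's order of events: no, because the period fixes the arm.
- The correction for changes in treatment: it concerns care, not who enrols.
- Intention to treat: it acts only after inclusion.
- The physician's grading before CRP is known: it tests the add-on value of CRP, not comparability of the periods.
- Mantel-Haenszel: it could be stratified by centre, but no stratum is named, and centre strata leave a within-centre shift between periods untouched.
- Identical eligibility criteria: they limit selection but do not govern who is approached or agrees.

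**3. Illustration with no true effect.** Taken from the document: 17% overall and 525 per group. Assumed, not in the document: 25% of control-period patients are high risk, with an event rate of 30% or 35%. The others then have (0.17 − 0.25·0.30)/0.75 = 12.7% or (0.17 − 0.25·0.35)/0.75 = 11.0%. Let the high-risk share be 20% or 15% in the PRECious period.

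PRECious-period rate: p₂ = share·high + (1 − share)·low.

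Chance of two-sided p < 0.05 favouring PRECious: Φ[(0.17 − p₂ − 1.96·SE₀)/SE₁], where SE₀ = √(2·p̄(1 − p̄)/525), p̄ is the mean of the two rates, and SE₁ is the unpooled standard error.

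| High-risk rate | Share in PRECious period | p₂ | Spurious fall (points) | Part of the 6-point target | Chance of a false benefit |
|---|---|---|---|---|---|
| either | 25% | 17.0% | 0 | 0% | 2.5% |
| 30% | 20% | 16.1% | 0.9 | 14% | 5.7% |
| 30% | 15% | 15.3% | 1.7 | 29% | 11.6% |
| 35% | 20% | 15.8% | 1.2 | 20% | 7.6% |
| 35% | 15% | 14.6% | 2.4 | 40% | 18.6% |

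Last row in full: p̄ = 0.158, SE₀ = 0.0225, (0.024 − 1.96·0.0225)/0.0225 ≈ −0.89, and Φ(−0.89) ≈ 0.19.

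**4. The opposite shift, with the planned effect real.** Let the high-risk share rise to 30% or 35% in the PRECious period, and let the algorithm multiply every risk by 11/17 (assumed proportional). The no-effect rate becomes 17.9% or 18.7% (high-risk rate 30%), or 18.2% or 19.4% (high-risk rate 35%). Multiplied by 11/17 this gives 11.6%, 12.1%, 11.8% and 12.6%. Power against 17% falls from 80% to 71%, 61%, 67% and 53%.

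**5. Would recorded baseline data show the shift?** If the risk factor is recorded, a share of 25% against 20% reaches p < 0.05 in a baseline comparison about 49% of the time, and 25% against 15% about 98% of the time.

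**The case against.** The strongest reply is that the document shows opportunity, not occurrence. No passage supports a shift of this size or direction. Surgeons might equally enrol more high-risk patients once systematic monitoring is in place. The renal-function and contrast-allergy exclusions apply in both periods and remove the most obvious CT-related selection equally. The chi-square sentence is generic, and covariate sets and screening logs commonly sit in a full protocol or analysis plan that is not shown. All of this stands as a limit on size and certainty. It does not remove the point, which rests on what the article does fix: recruitment into known periods, comparison by period, and named tests without covariates.

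Three stronger readings are tempting, and the document does not support them:

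- **That the trial could neither detect nor correct such selection.** Table 1 lists baseline variables in both groups, so measured imbalance could be seen and adjusted for (step 5). Only selection on unrecorded factors would escape.
- **That consent is taken on admission, or differently in each period.** The text places inclusion at admission, after consent; Table 1 places consent at pre-operative enrolment. No difference between periods is shown.
- **That only second-period patients accept routine blood sampling.** The Standard group section makes blood sampling on demand, but Table 1 lists CRP on postoperative days 2 to 5 for controls too. The document conflicts with itself here, so the point rests on the CT difference instead.

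**Conclusion.** The point holds in a bounded form. Individual consent into open-label periods that determine the arm lets case mix differ between the groups, and the tests named in the article would read such a difference as an effect or let it mask one. The direction is unknown.

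Under the assumed figures, a 5 to 10 point change in a 25% high-risk share moves the event rate by 0.9 to 2.4 points. That raises the chance of a false benefit from 2.5% to about 6–19%, or cuts power from 80% to about 53–71% if the shift runs the other way. These are illustrations, not predictions. A reader might infer that the result will be biased towards PRECious; the document does not show that.

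**What to change.** In Data collection and statistics, make the primary comparison a model adjusted for centre and for a short, prespecified set of baseline risk factors (such as age, ASA class and organ resected). Take these from the baseline variables that Table 1 already lists for both groups. Keep the crude test as supportive, and report baseline case mix by period and centre.

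The cost is slightly more analysis work. The limit is that adjustment removes only measured differences. Optionally, each centre could keep a brief count by period of eligible patients not included, at the price of some administrative time. The Trial status section says recruitment has not begun, so the change can still be prespecified.

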## Methods

### Study objectives

The aim of this study is to evaluate the role of a standardized quality control algorithm after MAS in order to early diagnose and treat major complications and achieve safe discharge criteria. The PRECious trial is a prospective, multicenter, open, stepped-wedge study. All patients who are planned to undergo elective major digestive surgery, defined as any gastro-intestinal resection with reconstruction via anastomosis or stoma, will be included. Our hypothesis is that the standardized postoperative quality control algorithm will allow for early diagnosis and treatment of complications, thereby decreasing morbidity and mortality associated with MAS.

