#### PRECious group

The second period will be considered the intervention group. All patients will be allocated to postoperative controls according to the PRECious protocol. Within this protocol peripheral blood samples for CRP measurements will be collected routinely on POD 2, 3, 4 and 5. If CRP exceeds 140 mg/L on the third, fourth or fifth POD, enhanced CT of the abdomen will be conducted within 24 hours. It is expected that two thirds of patients will undergo CT versus one third of the control group. Intravenous contrast is administered, with regard to renal function, to conduct CT. Depending on the organ undergoing surgery, oral or rectal contrast will be administered, for which the patient will have to drink oral contrast or receive rectal administration prior to CT. After the first postoperative week, CRP samples will be collected on demand, according to the consulting physician. If a major complication is diagnosed, immediate treatment will be commenced as soon as possible and as appropriate. All major complications are to be confirmed in reoperation or suspicious drain fluid upon percutaneous drainage and culture.

To allow for correct implementation of the protocol a transition period of month is deemed necessary before starting measurements in the intervention group. A flow-chart depicting the design of the study is displayed in Fig. 1.

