## Discussion

In an era of advancements in surgical techniques and fast-track care, both modalities aiming to decrease morbidity and mortality after major abdominal surgery, there is currently no postoperative quality control algorithm available. A quality control algorithm should aim at safe discharge and early diagnosis and treatment of complications [10, 12]. Den Dulk et al. demonstrated a decrease in the time taken to diagnose anastomotic leakage, by implementing a leakage score. Although no significant difference in mortality rates was observed (39 % versus 24 %; *p* = 0.24), their research supports the use of a postoperative quality control algorithm, although the optimal algorithm is yet to be determined [6, 7].

CRP has shown promising in multiple observational studies, with an optimal cutoff in our observational cohort study of 399 patients of 140 mg/L on the third POD [8, 20, 23, 27–29, 31, 41]. Information on the predictive value of dynamic changes in CRP is not available, but will be monitored, comparing the levels on POD 2 to 5. POD 1 levels are not measured, because a peak is not observed until POD 2 [23].

The effect of standardized measurement of CRP levels on diagnosis of postoperative complications has yet to be determined. Here we propose a standardized postoperative quality control algorithm including repeated CRP measures and additional CT if CRP levels exceed 140 mg/L on the third, fourth and fifth POD [2]. Aiming for a decrease in morbidity and mortality associated with major complications after major abdominal surgery a prospective, randomized study is deemed necessary.

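### The trial labelled stepped-wedge is described as one common switch from control to intervention, so an unmeasured trend over time cannot be told apart from the PRECious effect

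*Protocol article*

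**What the plan says.** The label is stepped-wedge throughout: in the abstract, in the Fig. 1 caption and in Study objectives ("The PRECious trial is a prospective, multicenter, open, stepped-wedge study").

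The account of allocation is different:

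- Standard group: "In the first period all patients will be allocated to the control group".
- Patient allocation and design: "After a transition phase of one month allowing for implementation, all patients will be allocated to the intervention arm".
- PRECious group: "The second period will be considered the intervention group. All patients will be allocated to postoperative controls according to the PRECious protocol".
- Patient allocation and design, on the comparison: "Thus, the two groups will be compared according to two periods".

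That same section sets aside a parallel-randomised design. It also rejects cluster allocation ("A cluster design is not deemed feasible due to differences between the participating centers") and then adopts a stepped wedge, which is itself a form of cluster design. On time trends it says "Due to the large number of participating centers, little bias is expected from other changes in treatment", and adds that changes will be monitored and corrected for where applicable. Participating surgeons and clinics lists seven hospitals.

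Power of the study gives 525 per group for 17% against 11%, with a two-sided Mantel-Haenszel test at 0.05 and 80% power. Data collection and statistics compares frequencies by Chi-square or McNemar tests. The Discussion closes by saying that "a prospective, randomized study is deemed necessary".

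**The concern.** A stepped wedge can support a causal claim because hospitals cross over at different, randomly ordered dates. In most calendar periods some hospitals are still in control while others have switched, and that contrast is what separates the intervention from the passage of time. With one common switch there are no concurrent controls, so period and treatment are the same variable.

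The safeguard offered is the number of centres. Many centres average out changes peculiar to single hospitals. They do not average out a change that reaches all of them together, whether there are seven or seventy. The Discussion itself describes ongoing advances in surgical technique and fast-track care that aim to lower morbidity and mortality, which is the kind of shared trend at issue. Growing familiarity with CRP and CT would be another.

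At stake is the hypothesis in Study objectives, that the algorithm decreases morbidity and mortality. The planned difference is 6 percentage points, so a background change of a few points matters in either direction.

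**Working it through.** **Inputs from the protocol article.** Control rate 17%, intervention rate 11%, 525 per group, two-sided alpha 0.05, power 80% (Power of the study); seven hospitals (Participating surgeons and clinics). The article gives no intracluster correlation (ICC), number of steps or size of secular trend. Those values below are assumptions.

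**1. The plan's own figure.** Two independent proportions, pooled variance under the null, no continuity correction:

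n = [1.960·√(2·0.14·0.86) + 0.842·√(0.17·0.83 + 0.11·0.89)]² / 0.06² = 523.8, so 524 per group.

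Power at 525 per group is 80.1%. The stated 525 is reproduced as a plain two-sample comparison, with no period or cluster term.

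**2. Can treatment be separated from period?** Take a model with a term for period 1, a term for period 2 and a treatment term. With all seven hospitals coded (0, 1), the treatment column equals the period 2 column: rank 2 for 3 parameters. The treatment effect is not identified once period is free, whatever the number of hospitals. With seven hospitals switching one at a time over eight periods, the rank is 9 for 9 parameters and the effect is identified.

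**3. What a shared drift does to the two-sample test.** No PRECious effect, 525 per period, rate falling from p₁ = 0.17 to p₂ for other reasons. With p̄ the mean of the two rates:

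- SE₀ = √(2·p̄(1−p̄)/525)
- SE₁ = √(p₁(1−p₁)/525 + p₂(1−p₂)/525)
- rejection probability = Φ[(d − 1.960·SE₀)/SE₁] + Φ[(−d − 1.960·SE₀)/SE₁], where d = p₁ − p₂

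For d = 0.02: SE₀ = 0.02263 and SE₁ = 0.02262, which gives Φ(−1.076) + Φ(−2.845) = 0.141 + 0.002 = 0.143.

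| Assumed background fall | Two-sided p<0.05 with no effect |
|---|---|
| 0 points | 5.0% |
| 1 point | 7.2% |
| 2 points | 14.3% |
| 3 points | 26.9% |
| 4 points | 44.2% |

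Drift the other way hides a real effect. If the true effect is 6 points and the background rate rises by 1, 2 or 3 points, power falls from 80% to 63%, 44% or 27%.

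**4. Power if a true stepped wedge is meant.** Assumed layout: seven hospitals, one per step, eight periods, equal cell sizes, mean rate 14%, period effects and a random centre effect fitted (Hussey-Hughes variance), difference 0.06. Power = Φ(0.06/SE − 1.960).

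At ICC 0 and 1,050 patients, the variance is 1.75 times that of the two-sample comparison. SE = 0.02142·√1.75 = 0.02833, 0.06/0.02833 = 2.118, and power = Φ(0.158) = 56%.

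| Assumed ICC | Power at 1,050 patients | Total for 80% power (approx.) |
|---|---|---|
| 0 | 56% | 1,840 |
| 0.001 | 54% | 2,040 |
| 0.01 | 45% | 2,800 |
| 0.05 | 40% | 3,010 |

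**The case against.** The strongest reply is that the article is condensed. Fig. 1, captioned as the flow chart of the stepped wedge, and protocol version 2.0 are not available. The one-month transition could be meant per hospital. Each hospital's board must approve before inclusion, so start and switch dates may differ. The online module returns the type of control protocol at each inclusion, which would fit hospital-specific switching. This stands as a limit: the point concerns the text as written, and a reader should not infer that staggering is known to be absent. It does not clear the text, because the abstract and the three Methods sections agree on a single switch. If hospitals do stagger, the article misdescribes the design, and Chi-square or McNemar tests would still leave time partly confounded with treatment.

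A reader might also infer that no analysis could help. That goes too far. Baseline and operative data are collected, so measured case-mix changes can be adjusted for, and the promise to correct for changes is weak rather than empty. What cannot be corrected is unmeasured change common to all hospitals.

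Nor does the article clearly present the trial as randomised. The word describes the study said to be needed, once, in the Discussion. The design statements do not use it, and the allocation section says that parallel randomisation is not preferred. It is a wording conflict and not the core of the point.

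Finally, the drifts are hypothetical. The article gives no evidence of a trend of any particular size.

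**Conclusion.** The point holds for the text as written. The stepped-wedge label implies concurrent controls that the described allocation does not provide, and the argument from the number of centres cannot replace them. What is described is an uncontrolled before-after comparison, which can be adjusted for measured case mix but not for an unmeasured shared trend.

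The false-positive figures show how sensitive the two-sample comparison is to drifts that are assumed. They do not measure a bias in this trial. The stepped-wedge power figures rest on the assumed ICCs and on one hospital per step. Even at ICC 0, that layout falls well short of 80% with 1,050 patients. The sample size arithmetic is correct for the two-sample test it uses; the difficulty is the design to which it is applied.

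**What to change.** Choose one of two designs and make the text agree with it.

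- **Keep the single switch.** Delete the stepped-wedge label and the randomised wording in the Discussion. Remove the statement that the number of centres makes bias small. Limit the conclusion to a before-after association adjusted for measured case mix. The cost is wording and a weaker claim; no extra patients are needed for this.
- **Run a true stepped wedge.** State the staggered crossover dates and the randomised order of the seven hospitals, with the one-month transition at each hospital left out of the analysis. Replace the Chi-square or McNemar comparison of the primary endpoint with a model that has period and centre terms. Restate the power with a declared ICC and number of steps. A reader might think staggering costs only a rollout calendar, but it is not free if 80% power is to be kept: under the layout above the total rises from 1,050 to roughly 1,840 to 3,010.

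The article says that the trial is not yet recruiting and that each hospital's board has still to approve the protocol before inclusion, so the choice can be made now. After a common switch, concurrent control data cannot be recovered.
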